### Exclusion criteria

Exclusion criteria are limited to patients: (1) aged < 18 years or > 80 years; (2) diseases receiving preceding systemic therapy with glucocorticoids, such as chronic kidney disease, inflammatory disease, or other immune system related diseases; (3) anesthesiologist judge that the subjects cannot use the dexamethasone, such as diagnosed with epilepsy or active ulcer; (4) intraoperative findings of extra-hepatic disease before intervention, need to undergo a synchronous resection for other organs except gallbladder; (5) intraoperative findings of additional lesions before intervention, need to combine with other procedures, such as ablation or bilo-enteric anastomosis; (6) unable to provide informed consent.

### Follow-up management and withdraw criteria

We will develop a rigorous follow-up plan to improve the follow-up rate and ensure data quality. Plans are as follows: (1) for subjects: excluding patients with inconsistent family opinions and unwillingness to be included in the screening process, strengthening subjects’ education in the informed consent process, and promoting communication with subjects of the time and content of review after the surgery and physical state after discharge; (2) for researchers: introducing dedicated personnel for follow-up management and dealing with the follow-up tables; (3) for information management: applying app software for follow-up management, developing a personalized follow-up management system. E-visit, a platform focused on patient clinical trials, supports patient original case upload, patient outcome report, follow-up management and doctor-patient interaction, various message reminders, and so on.

Participants will be allowed or required to withdraw from the RCT if the following are met: (1) they do not follow the treatment plan strictly (such as refusing continuous 7 days of collecting blood sample, receiving the targeted therapy or immunotherapy after surgery) while participating in the RCT, and (2) subjects are required to leave the RCT, such as participants cannot accept continuous 7 days of collecting blood sample or postoperative follow-up. For participants who withdraw from the RCT, we plan to record some routine postoperative testing indicators, including hepatocellular injury parameters (ALT, AST, and their peak value) and liver function indexes (TBil and international normalized ratio (INR)). Besides, postoperative complications, postoperative hospital stay, and 30- and 90-day mortalities are also recorded. However, these data will not be analyzed.

### Randomization and blinding

Once informed consent is provided, patients will be assigned randomly in a 1:1 ratio to the dexamethasone group or the control group on the day when they accept surgery. The computer-generated numbers are prepared by a research statistician and kept inside sealed envelopes by a research assistant who is not physically present in the operating room. Block size will not be disclosed to preserve allocation concealment.

When the patient enters the operating room, a research assistant will open the corresponding opaque envelope containing the patient allocation status and assigned medication. Then, the research assistant will refer the assigned medication to the anesthesiologist and remind them to inject the medication 10 min before IPM. The medication container, appearance, dosage, and technique of administration will be the same for two groups. Patients, surgeons, nursing team, anesthesiologists, and outcome assessors will be blinded to the study allocation status. If there is a situation such as a medical need or emergency which required unblinding, the principal investigator will be informed and make the final decision and report to the ethics committee.

### Intervention

Perioperative care and intraoperative technique for both study groups follow the routine practice of the surgical team. Patients in the dexamethasone group will receive intravenous administration of 10 mg dexamethasone (dexamethasone sodium phosphate injection, 1 ml:5 mg) 10 min before IPM. Patients in the control group will receive intravenous administration of 2 ml saline 10 min before IPM. All the patients will get routine postoperative rehabilitation management, and their relevant concomitant cares are homologous.

### Operative procedure

A low central venous pressure anesthesia (below 5 cmH_2_O) is required for hepatectomy. The types of incision include inverse L-shape under the right costal margin or “laparoscopic five hole.” Intraoperative ultrasound is routinely performed to identify, count, and characterize the nature and vascular proximity of the tumor. IPM is performed at the hepatoduodenal ligament using a rubber sling for both open and laparoscopic hepatectomy. The liver parenchyma is dissected by harmonic scalpel (Ethicon Endo-Surgery, Cincinnati, OH), and hemostasis is achieved with dipolar coagulation, clips, or suturing for either open or laparoscopic hepatectomy [10].

### Data collection

An outcome assessor will collect data from electronic medical record systems. All participants will be diagnosed with HCC at the outpatient clinic of West China Hospital of Sichuan University for the first time. Our planned recruitment period is from December 3, 2022, to April 1, 2023, with a postoperative follow-up of 3 months.

Demographic data:Age, yearGender, male/femaleBody mass index, kg/m^2^Comorbid conditionsLiver disease background

Preoperative laboratory tests:Hepatitis B surface antigen positivity, *n* (%)Hepatitis B virus deoxyribonucleic acid ≥ 1000 IU/ml, *n* (%)Alpha-fetoprotein ≥ 400 ng/mL, *n* (%)TBil level, μmol/LALT level, IU/LAST level, IU/LAlbumin level, g/LINRPlatelet count, 10^9^/LCRP level, mg/LIL-6 level, pg/mlProcalcitonin (PCT) level, ng/mlChild-Pugh grade A, *n* (%)Indocyanine green retention rate at 15 min ≤ 10%, *n* (%)Portal hypertension, *n* (%): defined as esophageal varices detected by endoscopy or a splenomegaly (major diameter > 12 cm) with a platelet count < 100,000/mm^3^ [20]

Intraoperative parameters:Tumor number, *n*Tumor size, cmTotal operation time, minNo. of the cycle of IPM, *n*Transection time, minTransection area, cm^2^: calculated the grids that the liver sections print on grid paperTotal blood loss, ml: assessed by the extraction of blood in the suction apparatus subtract the amount of saline used for intraoperative irrigation plus the assessment amount of blood in the gauze roll (by weighting the soaked gauzes)No. of blood transfusion, *n* (%)Units of red blood cell transfusion, UOpen/laparoscopic hepatectomy, *n*/*n*Type of resection: wedge resection, left lateral sectionectomy, right posterior sectionectomy, segmentectomy, bisegmentectomy, trisectionectomy, left hemi-hepatectomy, right hemi-hepatectomy, extended left/right hepatectomyMinor/major hepatectomy, *n*/*n*: defined as major when three or more segments are resected [21]

Postoperative laboratory parameters:Peak ALT, IU/LPeak AST, IU/LAUC_ALT_, U/(L×d)AUC_AST_, U/( L×d)Peak TBil, μmol/LPeak INRPeak CRP, mg/LPeak IL-6, pg/mlPeak PCT, ng/ml

Pathological data:Microvascular invasion, *n* (%)Tumor grade, *n* (%): G1, G2, G3-4Presence of fibrosis, *n* (%)Fibrosis stage, *n* (%): early (Ishak 1–2), intermediate (Ishak 3–4), advanced; cirrhosis (Ishak 5–6)

Postoperative follow-up data: surgeons and outcome assessor will jointly evaluate patients for postoperative complications and be blinded to the study allocation status of patients.Specific complications:* Liver failure: defined according to the “50-50 criteria” on postoperative day (POD) 5 [22]* Hemorrhage: defined as a postoperative hemoglobin level dropping more than 3 g/dL compared to the postoperative baseline level [23]* Bile leak: determined by an increase in bilirubin concentration in abdominal drainage of more than 3 times compared to that in serum on POD 3 [24]* Ascites: identified according to postoperative daily drainage fluid more than 10 mL/kg of body weight [25]* Pleural effusion: if symptomatic or requiring thoracocentesis or drainage* Incision site infection: if symptomatic or secretion culture positive* Other infections: diagnosed by responding clinical manifestation and etiological results* Other complications: classified and recorded according to the Clavien–Dindo grade [26]

Adverse events (AE) and serious adverse events (SAE)No. of entering into intensive care unit, *n*Postoperative hospital stay, day30-, 90-day mortality, *n* (%)

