### Outcome measures

All blood samples will be collected on PODs 1, 2, 3, 4, 5, 6, and 7 following the same procedure for performing serial laboratory evaluation. All blood samples will be collected at 7 a.m. every day, which then will be sent by the outcome assessor to the Department of Experimental Medicine for examining by a fixed physician. Preoperative laboratory parameters are viewed as baseline of postoperative laboratory parameters (if the postoperative stay is not more than 7 days, outcome assessors will be responsible for the subjects for blood sample collection).

Primary outcomes are as follows: peaks value of ALT and AST and AUC of ALT and AST.

Indicators of hepatocellular injury are as follows: ALT and AST of postoperative 7-day both the two groups; then, we will calculate the mean for postoperative 7-day after surgery to depict the line charts with mean ± stand error.

Peak values of ALT and AST as well as AUC values of the postoperative 7-day course of ALT and AST (peak value is defined as the maximum value measured in 7 days, and AUC is calculated by the value of postoperative 7 days). The magnitude of the effect of glucocorticoids on relieving surgical pressure and alleviating ischemia-reperfusion injury are assessed by the AUC surrounded by continuous ALT and AST, which is the metrics for declaring superiority of the tested intervention.

We decided that peaks value of ALT and AST and AUC of ALT and AST were primary outcomes after 16 July 2023.

Secondary outcomes:Intraoperative blood lossLiver function: assessed by measuring serum level of TBil and INR for coagulationInflammatory cytokines: assessed by IL-6, PCT, CRP, and their respective peaksPostoperative complications: according to the Clavien–Dindo grade, including major complications and minor complicationsPostoperative hospital staysMortality: defined as in-hospital death or death within 30 or 90 days after surgery

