### Sample size

This trial is originally conceived by the statistical and clinical teams with a total of 270 patients (135 within each group). It is based on our previous RCT [10] and the other relative RCT in our center [27]. In our previous study, the standard deviation (*σ*) of the postoperative serum peak ALT value is 184.684, AST value is 141.1 between two groups, and the target difference (*δ*) is 58.882 IU/L. The sample size calculated using peak ALT value is larger than using peak AST value. Thus, we estimate a sample size of 135 patients in each group to achieve an 80% statistical power (Uβ = 0.84, 1-sided test) at the 5% significance level (Uα = 1.645, 1-sided test) as well as an estimated dropout rate of approximately 10%.

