Of course, we also knowledge that preoperative steroids administration may arise some negative effects, such as inhibition of liver regeneration, gastrointestinal bleeding, and infection. However, Glanemann et al. have demonstrated that preoperative steroids administration has no apparent effects on hepatic regeneration [32]. Furthermore, liver regeneration has a close relationship with IL-6 that the overproduction of IL-6 inhibits liver regeneration [33]. As for gastrointestinal bleeding, dexamethasone administration should be cautious in patients after hepatectomy [34]. We will routinely use proton pump inhibitors. Administration of glucocorticoids may cause postoperative infections due to elevation of blood glucose. However, a recent RCT demonstrates that administration of preoperative single-dose methylprednisolone in patients undergoing a subsequent major liver resection lowers the risk of postoperative complications and surgical site infections as well as results in a shorter length of hospital stay [35]. Therefore, the trial protocol is reasonable and the results of the trial may be clinically significant.

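### The named hemorrhage item rests on a hemoglobin fall alone, so some bleeds treated by transfusion or re-intervention will not be counted as hemorrhage

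*Protocol article*

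**What the plan says.** The list of specific complications under Data collection defines hemorrhage as "a postoperative hemoglobin level dropping more than 3 g/dL", measured against a postoperative baseline and citing reference 23. No alternative criterion follows. The red-cell transfusion items (number transfused, units) stand under intraoperative parameters in the same section and are not linked to the hemorrhage item.

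The neighbouring item for effusion works differently and counts treatment: "Pleural effusion: if symptomatic or requiring thoracocentesis or drainage". A residual item covers events outside the named definitions: "Other complications: classified and recorded according to the Clavien–Dindo grade". Adverse events, serious adverse events and intensive care admissions are recorded as well.

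Under Outcome measures, the secondary outcome is postoperative complications by Clavien-Dindo grade, major and minor. On bleeding as a harm of the study drug, the Discussion says: "As for gastrointestinal bleeding, dexamethasone administration should be cautious in patients after hepatectomy".

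**The concern.** The criterion reads the raw hemoglobin value, and the response to a bleed changes that value. Transfusion lifts it, and an endoscopic, radiological or surgical procedure halts its fall. A bleed serious enough to be treated promptly may thus fail the definition because it was treated.

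At stake is the hemorrhage row in the comparison of complications. It is the only bleeding-specific complication defined in the list, so a reader will look there for a bleeding harm. If a share of treated bleeds is missing, the row rests on fewer events and describes bleeding incompletely.

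**Working it through.** **The plan's own figure.** The documents give no hemorrhage rate, so there is none to reproduce. The only computed figure is the sample size. Its inputs, from the Sample size section, are: "the standard deviation (*σ*) of the postoperative serum peak ALT value is 184.684"; "the target difference (*δ*) is 58.882 IU/L"; one-sided 5% (1.645); 80% power (0.84); about 10% dropout. Then n = 2 × ((1.645 + 0.84) × 184.684 / 58.882)² = 121.5 per group, and 121.5 / 0.9 = 135.0. The stated 135 reproduces and does not depend on the hemorrhage definition.

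**The rule applied to three invented patients.**

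| Patient | Course | Largest recorded fall | Scored as hemorrhage? |
|---|---|---|---|
| A | Baseline 10.5 g/dL, falls to 7.8, transfused, rebleeds to 8.0 | 10.5 − 7.8 = 2.7 | No |
| B | Visible drain bleeding, re-operated at a fall of 2 g/dL | 2.0 | No |
| C | 13.5 to 10.4 g/dL, no treatment | 13.5 − 10.4 = 3.1 | Yes |

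A and B show the gap: both were treated for bleeding and neither meets the definition. C is a different matter, a fall that counts without any treatment. Adding criteria does not change C.

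**How large the undercount could be (assumptions only).** Hemoglobin levels and transfusion practice are not in the documents. Suppose transfusion follows whenever hemoglobin is below T. With slow bleeding and frequent checks, a patient whose baseline is below T + 3 never shows a fall above 3. For a normal baseline with mean μ and SD 1.3, the missed share is then Φ((T + 3 − μ) / 1.3). For T = 8 and μ = 11.5 this is Φ(−0.385) = 35%.

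Simulated bleeders had a true loss of 3 to 6 g/dL, with 2 units at each sub-threshold check and a gain of 0.5 to 1.0 g/dL per unit. Share of true bleeds missed at T = 8:

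| Loss between checks | Mean baseline 12.5 | 11.5 | 10.5 |
|---|---|---|---|
| 0.5 or 1.0 g/dL | 12% | 35% | 65% |
| 2 g/dL | 2–3% | 8–12% | 23–35% |
| More than 3 g/dL before any transfusion | 0% | 0% | 0% |

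For T from 7 to 9, the slow-bleeding case runs from 3% to 88%. The answer depends almost wholly on how fast patients bleed, how often they are checked, and where they start.

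**In events.** If 5% of 270 patients truly bled, that is 0.05 × 270 = 13.5 events. If 25% to 50% were treated before the fall passed 3 g/dL, 13.5 × 0.75 = 10.1 down to 13.5 × 0.50 = 6.8 would be counted. Both the 5% and the 25% to 50% are assumptions.

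**The case against.** The strongest reply is that a treated bleed has other routes into the data. The secondary outcome is the Clavien-Dindo grade of complications, not the hemorrhage label. There is the residual complications item, adverse event reporting, and, under Safety and participant compensation, recording of treatment until an event resolves. This stands: the event need not vanish from the overall complication count. It does not repair the hemorrhage row, which would still be short.

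A reader might infer that a true excess of bleeding on dexamethasone would go unseen. The documents do not support that. Surgeons and outcome assessors are blinded, the same rule applies to both groups, and no difference in error between groups is shown. Gastrointestinal bleeds can also be recorded outside the hemoglobin item. A reader might also infer that cirrhotic patients are undercounted most. A lower starting hemoglobin does make a miss more likely in the slow-bleeding model, but no hemoglobin data by cirrhosis status are given.

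The definition cites a source that is not at hand, and the article condenses a fuller protocol. Either may hold further criteria. That cannot be checked, so the point rests on the definition as printed. Finally, secondary outcomes are tested only after superiority on the primary outcomes. That limits the weight of the point but does not remove it, since complications may also be summarised descriptively.

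**Conclusion.** The point holds as a misclassification in one named complication. As written, the definition leaves out bleeds that were treated before hemoglobin fell by more than 3 g/dL, and nothing else in the item brings them back. The direction is clear: treatment can only hide events under this rule.

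The size is unknown. The figures above illustrate a mechanism; quoting 3% to 88% as an estimate for this trial would go beyond the documents, because that range presumes slow bleeding with close checking, and brisk loss takes it to zero. Outcome measures describes one blood draw a day, at 7 a.m.

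No primary outcome, sample size or significance level is affected. The item merits correction because bleeding is a harm the protocol itself names and the correction is cheap.

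**What to change.** Classify hemorrhage as any one of: (1) a hemoglobin fall of more than 3 g/dL, as now; (2) postoperative red-cell transfusion given for bleeding or falling hemoglobin; (3) any endoscopic, radiological or surgical intervention for bleeding. Extract postoperative red-cell units with dates, and re-interventions, from the electronic record that already serves as the data source. This changes how an outcome is classified, not how patients are treated.

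Trial status gives follow-up complete on 1 July 2023 and unblinding on 16 July 2023, so the definition cannot be replaced as if prespecified. Report the written definition as planned. Show the extended one beside it, labelled as a post hoc supplementary analysis, applied to both groups by assessors unaware of allocation.

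The cost is one sentence of definition and a small extra extraction. The hemorrhage rate will be somewhat higher, and untreated falls above 3 g/dL, such as Patient C's, will still count.

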### Outcome measures

All blood samples will be collected on PODs 1, 2, 3, 4, 5, 6, and 7 following the same procedure for performing serial laboratory evaluation. All blood samples will be collected at 7 a.m. every day, which then will be sent by the outcome assessor to the Department of Experimental Medicine for examining by a fixed physician. Preoperative laboratory parameters are viewed as baseline of postoperative laboratory parameters (if the postoperative stay is not more than 7 days, outcome assessors will be responsible for the subjects for blood sample collection).

Primary outcomes are as follows: peaks value of ALT and AST and AUC of ALT and AST.

Indicators of hepatocellular injury are as follows: ALT and AST of postoperative 7-day both the two groups; then, we will calculate the mean for postoperative 7-day after surgery to depict the line charts with mean ± stand error.

Peak values of ALT and AST as well as AUC values of the postoperative 7-day course of ALT and AST (peak value is defined as the maximum value measured in 7 days, and AUC is calculated by the value of postoperative 7 days). The magnitude of the effect of glucocorticoids on relieving surgical pressure and alleviating ischemia-reperfusion injury are assessed by the AUC surrounded by continuous ALT and AST, which is the metrics for declaring superiority of the tested intervention.

We decided that peaks value of ALT and AST and AUC of ALT and AST were primary outcomes after 16 July 2023.

Secondary outcomes:Intraoperative blood lossLiver function: assessed by measuring serum level of TBil and INR for coagulationInflammatory cytokines: assessed by IL-6, PCT, CRP, and their respective peaksPostoperative complications: according to the Clavien–Dindo grade, including major complications and minor complicationsPostoperative hospital staysMortality: defined as in-hospital death or death within 30 or 90 days after surgery

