### Statistical analysis

The trial is designed to test the superiority of dexamethasone to placebo with respect to the primary outcomes and secondary outcomes with the use of difference analysis. Superiority with respect to the primary outcomes are required before the secondary outcomes could be tested. All included participants will provide 80% power to detect superiority with respect to the primary outcomes. The AUC of ALT and AST will be tested for superiority, analyzed by Student’s *T* test or the Mann-Whitney *U* test.

Continuous variables will be presented as the mean ± standard deviation or median with its range based on normality testing and compared by an independent sample Student’s *T* test or the Mann-Whitney *U* test. Categorical variables will be presented as number (percentage) and compared using chi-square test or Fisher exact test. The modified intention-to-treat (ITT) principled analysis is applied for allocating patients into the group; moreover, when compliance is at a low level or the trial is no longer double-blinded, the as-treated (AT) analysis will be added to be supplements. Sensitivity analysis of missing data (loss to follow-up, death, withdrawal, etc.) will be conducted with the multiple-imputation approach. All tests for differences except primary outcomes are two-tailed and considered statistically significant if *P* values < 0.05. Bonferroni correction will be performed to correct for four primary outcomes statistically. We have changed the adjustment for multiple testing after 16 July 2023. All statistical analyses are performed by the SPSS version 20 and GraphPad Prism version 8.0.1.

As appropriate, the significance of postoperative categorical complications will be analyzed using chi-square test or Fisher exact test or will be tabulated and summarized using descriptive statistics.

Besides, according to the extent of resection and background of hepatic fibrosis after surgery, subgroup analysis will be performed to assess the protective effect of administration of dexamethasone before clamping the hilar pedicle on residual liver injury after undergoing liver resection with 25-min hepatic inflow occlusion.

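### The Outcome measures and Statistical analysis sections give inconsistent rules for declaring superiority (AUC alone, or four Bonferroni-corrected primaries), and the primaries and the correction were settled after unblinding

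*Protocol article*

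**What the plan says.** All statements are in the protocol article.

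- **Outcome measures, primary outcomes:** "Primary outcomes are as follows: peaks value of ALT and AST and AUC of ALT and AST". That makes four.
- **Outcome measures, two paragraphs on:** the size of the effect is to be judged by the AUC of ALT and AST, "which is the metrics for declaring superiority of the tested intervention".
- **Statistical analysis, first paragraph:** "The AUC of ALT and AST will be tested for superiority". The peaks are not named there.
- **Statistical analysis, gate:** "Superiority with respect to the primary outcomes are required before the secondary outcomes could be tested".
- **Statistical analysis, multiplicity:** "Bonferroni correction will be performed to correct for four primary outcomes statistically". The per-test level is not written out; 0.05/4 gives 0.0125.
- **Statistical analysis, secondaries:** "All tests for differences except primary outcomes are two-tailed and considered statistically significant if" P is below 0.05. No adjustment among them is given.
- **Timing:** Outcome measures dates the choice of the four primaries, and Statistical analysis dates the change in multiplicity adjustment, to after 16 July 2023. Trial status gives 16 July 2023 as the day of unblinding.

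**The concern.** A success rule has to say which outcomes count, how many must be won, and at what level. Here the first is answered in two ways. If only the AUCs decide, a correction over four gives half of the alpha to peaks that cannot declare superiority. If all four decide, the two sentences that single out AUC are wrong. The second is not answered: a Bonferroni split suits a rule that any one outcome suffices, while the gate's plural wording could mean that all are needed, in which case no split would be required.

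The readings can give opposite verdicts on the same data. Because the primaries and the correction were settled after unblinding, nothing in the text shows that the reading was fixed before results could be seen. The open rule also decides whether the secondary outcomes are tested at all.

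**Working it through.** **1. The plan's own figure.** Inputs from Sample size: SD 184.684 (peak ALT) and 141.1 (peak AST), difference 58.882 IU/L, one-sided z of 1.645 and 0.84, about 10% dropout.

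- Peak ALT: n = 2 × (1.645 + 0.84)² × (184.684/58.882)² = 2 × 6.1752 × 9.8377 = 121.5, so 122 per group.
- With dropout: 122 × 1.1 = 134.2, so 135; or 122/0.9 = 135.6, so 136. The stated 135 reproduces.
- Peak AST: 2 × 6.1752 × (141.1/58.882)² = 70.9, so 71. This agrees with "The sample size calculated using peak ALT value is larger than using peak AST value".

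**2. One data set, several verdicts.** Suppose one-sided P = 0.005 for peak ALT and 0.03 for each of the other three.

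| Reading | Verdict |
|---|---|
| Any of four at 0.0125 | positive |
| All four at 0.0125 | negative |
| AUCs at 0.0125 (Bonferroni over four) | negative |
| AUCs at 0.05 (no correction) | positive |

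**3. How far the rules differ.** Assumptions, because the article gives neither correlations nor an SD or difference for AUC: every outcome has the standardised effect of peak ALT, 58.882/184.684 = 0.319 SD; 121.5 evaluable per group; one common correlation ρ, taken from 0 to 0.95.

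- Mean of each test statistic: 0.319 × √(121.5/2) = 2.485.
- Critical values: 2.241 at 0.0125 and 1.645 at 0.05.
- One outcome at 0.0125: Φ(2.485 − 2.241) = 59.6%.
- At ρ = 0: any of four = 1 − (1 − 0.596)⁴ = 97%; all four = 0.596⁴ = 13%.
- For ρ > 0, with μ = 2.485 and critical value c: P(all) = ∫ φ(t) Φ((μ + √ρ t − c)/√(1−ρ))⁴ dt, and P(any) = 1 − ∫ φ(t) Φ((c − μ − √ρ t)/√(1−ρ))⁴ dt, integrated numerically. For the two AUCs the power is 2 in place of 4; for no effect, μ = 0.

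| | ρ = 0 | ρ = 0.8 | ρ = 0.95 |
|---|---|---|---|
| Effect present: any of four at 0.0125 | 97% | 77% | 68% |
| Effect present: all four at 0.0125 | 13% | 41% | 51% |
| These two rules disagree (any minus all) | 85% | 36% | 18% |
| No effect: any of four at 0.0125 | 4.9% | 3.0% | 2.1% |
| No effect: either AUC at 0.05 | 9.8% | 7.5% | 6.3% |

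**4. The gate.** With four tests at 0.0125, the chance of a false primary claim is at most 4 × 0.0125 = 5%, whether any, all or only the AUCs are required. It exceeds 5% only if either AUC suffices at an uncorrected 0.05. Once the gate is open, k independent true-null secondaries at 0.05 give at least one false positive with probability 1 − 0.95ᵏ: 23% for k = 5 and 40% for k = 10. Both k and independence are illustrative.

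**The case against.** The strongest defence is that the Statistical analysis sentence on AUC only names an outcome and its test. The next paragraph of that section gives the same tests for all continuous variables, which covers the peaks, and the Abstract assesses the primary endpoints by peaks as well as AUC. On that view only the Outcome measures sentence conflicts with four primaries. This narrows the conflict but does not remove it: that sentence expressly makes AUC the deciding metric, and the Bonferroni sentence expressly counts four.

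A second defence is that an article may leave the any-or-all rule and the per-test level to a fuller document. That is fair for those two details alone. It does not cover a rule that the article does state, and states inconsistently.

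The numbers are also illustrative. If the single difference of 58.882 applied to AST, its effect would be 58.882/141.1 = 0.417 SD. Giving both AST outcomes that effect at correlation 0.8 yields 91% for any of four and 49% for all four. The levels move, but the gap between the rules remains.

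Four stronger readings are tempting and are not supported:

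- **All versus any as a stated contradiction.** Neither word appears. Each is an inference, so this is an ambiguity.
- **A gate without any error rate.** If all four tests run at 0.0125, the chance of wrongly opening it when nothing differs is at most 5%.
- **A 40% overall false-positive risk.** That figure applies only after the gate opens, with ten independent null secondaries. If dexamethasone affects nothing, the Bonferroni gate also caps false secondary claims at about 5%.
- **Sizing on peak ALT as part of the conflict.** Peak ALT is a listed primary outcome. Whether AUC is adequately powered is a separate question.

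**Conclusion.** The concern stands in limited form. The two sections do not agree on whether AUC alone or four corrected outcomes declare superiority, and the gate leaves open how many primaries must be won. The choice matters: under the equal-effect assumption, any-of-four and all-four at 0.0125 reach opposite verdicts in 85% to 18% of trials for correlations from 0 to 0.95. Control of the primary-family error at 5% holds if the Bonferroni sentence governs, and fails (9.8% to 6.3%) if either AUC is tested uncorrected. Error among the secondaries is not controlled once the gate is open.

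The dates make this something to resolve before any claim of superiority. A reader might infer that the rule was picked to suit the results. The documents do not show that; they show only that the text offers no protection against it.

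**What to change.** 1. State the success rule that version V1.0 (4 November 2022) fixed before unblinding: which outcomes, all or any, at what level. Make Outcome measures and Statistical analysis agree with it, and label any departure as post hoc.
2. If V1.0 fixed no rule, keep all four primaries, test them by Holm at the stated overall one-sided 5% (steps 0.0125, 0.0167, 0.025, 0.05), report all four results, and remove the sentences that make AUC alone decisive. Holm is never less powerful than Bonferroni. In the example above it would reject peak ALT and then stop, since 0.03 exceeds 0.0167.
3. Report the secondaries descriptively. Alternatively, open the gate only when all four primaries are rejected and then apply a multiplicity adjustment among the secondaries. The stricter gate alone does not control error among them.
4. Do not newly select a single primary outcome now. After unblinding, that would itself be a post hoc choice.

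The cost is wording, and some secondary P values lose confirmatory status. No new data are needed.
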